### Randomization

#### Overview

Participants will be individually randomized (T_3_) using the King’s Clinical Trials Unit web-based randomization service upon completion of their baseline questionnaires (T_2_) by a research assistant. Online peer support requires a sufficiently large community of active users to enable discussions and foster a community. Therefore, we will allocate participants using a 2:1 ratio (100 to the intervention arm and 50 to the control arm). Treatment allocations will be stratified based on baseline depressive symptom severity using minimization with randomly varying block sizes. Baseline depressive symptom severity will be measured using the PHQ-8 total score (low=PHQ-8 score of <7; high=PHQ-8 score of ≥7). Although the research team will be unblinded to treatment allocations, the web-based system will conceal subsequent allocations.

#### Blinding

Due to the nature of the interventions, it is not possible to blind participants. As the baseline and mid- and postintervention assessments will be self-reported by participants via web-based Qualtrics questionnaires, the outcome assessments will not be blinded. All research team members, including the trial statistician and qualitative interviewers, will be unblinded to treatment allocation.

### Ethical Considerations

This feasibility study (and concurrent observational community cohort) has been approved by the South Central – Oxford C Research Ethics Committee (Integrated Research Application System ID328175). This study is sponsored by KCL. Approval for any amendments will be first sought from our sponsor (KCL) before submission and final approval from the South Central – Oxford C Research Ethics Committee. This trial has been registered on ClinicalTrials.gov (NCT06222346).

Informed consent will be collected on 2 occasions (Multimedia Appendix 3). Interested participants will first consent to the eligibility screenings (at T_1_ and T_2,_ separated by the wait period). If found to be eligible at the second screening, participants will then provide informed consent for the feasibility trial. Participants who consent to the trial will be remunerated with vouchers upon completion of the baseline (£10 [US $13.74]) and postintervention (£10 [US $13.74]) assessments. Those who participate in online interviews will be remunerated with a £20 (US $27.48) voucher. Participants can choose to withdraw from the intervention, or the entire trial, at any time. Those who withdraw from their allocated treatment arm (ie, removal of access to CommonGround or ceasing of the receipt of control emails) but wish to continue with data collection will be contacted to complete the mid- and postintervention questionnaires. Participants will be invited to share their reasons for withdrawal.

All participants will have their right to privacy, communicated and protected at all times. A privacy policy will be drafted for CommonGround. No identifiable information will be published in any output from this fRCT. We will outline our procedures to maintain confidentiality via our participant information sheet with participants before seeking their consent to participate. All individuals who complete the eligibility screenings will be randomly assigned a unique ID. All research data will be pseudonymized, password-protected, and held on secure servers. Data from the one-to-one online interviews or focus groups will be audio recorded and stored in password-protected files on KCL secure servers. Personal data in the form of audio files will also be shared with our transcription service, “Way with Words,” who will sign a nondisclosure agreement prior to listening to any recordings.

### Interventions

#### Intervention Arm: CommonGround

The CommonGround platform has been co-designed through collaboration with people with lived experience of long-term conditions, clinicians, academics, and web design experts. The “all diagnoses welcome” approach, driven by the experiences of our PPI group, aims to be inclusive of all people living with long-term conditions. The online platform has a community feed for forum discussions (peer support component) and a resource section, including evidenced-based self-help information (psychoeducational component). Following usability testing and prototype refinement in collaboration with our RAG (pending publication), CommonGround includes the key features and functions outlined in Textbox 1 [38] (refer to Multimedia Appendix 4 for screenshots).

All participants will be required to provide personal details (name, email address, mobile number, and date of birth) upon creating their account to allow the research team to verify their identities. As participants will be anonymous to one another in the community, they will be asked to create an anonymous pseudonym username. Throughout the intervention period, the research team will be available to assist with any technical or accessibility issues. Participants can engage with CommonGround as often as they wish (ie, participation is voluntary).

Key features and functions of the CommonGround platform.CommonGround is an online platform that is accessible via desktop and mobile devices. The platform has 2-factor authentication via SMS text message and automatic log-out after 10 minutes of inactivity.There is a discussion forum where users can create anonymous posts (eg, “How I am feeling”). Users can also react to (eg, “I hear you” or [laughter emoji]), comment on, and save forum posts.The platform includes an intuitive navigation bar that features a notification bell and a search tool to help users locate content of interest.Users have access to a private My Garden page, where they can store posts from other users and resources they have chosen to save.The Resources page gives access to evidence-based psychoeducational material on the mind-body link alongside self-help information and signposting to reputable resources and further support. The topics were selected for their relevance to people living with *any* long-term condition, such as advice on managing sleep, physical activity, and managing symptoms.Users have the ability to follow and mute other users, view other users’ profiles, and read their biography and view their recent activity.The platform includes an About Us page where users can read more about the research behind CommonGround, the platform itself, how to contact the research team, and technical troubleshooting (via “how-to” guides).There is a Crisis and Further Support page and web page banner where users can find organizations able to provide further support, particularly for crisis situations. This signposting is necessary because one-to-one and crisis support will not be offered on CommonGround.Dedicated administrative accounts will have access to an administrative panel and additional moderation functions that will allow our trained moderators to review, edit, and remove content from the community forum. The moderation team will be separate to the research team and solely dedicated to the safety of the platform. The moderators will mediate discussions between users and operate a “three-strike” policy whereby users repeatedly failing to adhere to the community principles (terms of use agreed to upon account creation) will be removed from the platform. Users can also flag posts to the attention of moderators. The moderation, safeguarding, and privacy policies that govern the operation of CommonGround will be clearly displayed on the platform. All policies have been coproduced with our coapplicant and based on guidance from King’s College London research and development and input from established organizations, including the online harms team from the Samaritans [38]. The community principles and moderation and safeguarding policies are available upon request from the corresponding author.There will be an engagement team (members of the research team) who will implement the engagement policy that has also been codeveloped with our patient and public involvement group and coapplicant. This policy includes weekly email circulars providing community updates and reminders to those who have not logged in recently. The engagement team will also have administrative accounts to encourage engagement via posts summarizing *trending* topics in the community feed and sharing relevant topics for people living with long-term conditions, which can be pinned to the top of the community feed. The engagement policy is available upon request from the corresponding author.

#### Control Group

From the launch date (T_4_), participants in the control arm will be sent fortnightly emails directing them toward the NHS mental health web pages, a series of web-based resources provided by the NHS [39]. These web pages are not specifically targeted at people living with long-term conditions. The web pages include information sheets and mental health support, including topics such as managing different life situations and events. In addition, there is a self-help section that includes guides, tools, and activities to support mental health. Participants can engage with the NHS content as often as they wish (ie, participation is voluntary).

#### Criteria for Discontinuing or Modifying Allocated Interventions and Posttrial Care

The intervention is intended to complement the usual care participants receive for their long-term conditions. Participants can withdraw from the intervention (complete follow-up assessments) or the entire trial at any time. There are no criteria for discontinuing or modifying allocated interventions. However, for participants in the intervention group, platform access will be removed in the event of severe violations of the community principles and in accordance with the moderation policy. As this feasibility trial is not powered to assess the potential benefits or safety of the platform, there are no planned provisions for ancillary or posttrial care, and all CommonGround accounts will be closed after 3 months (at T_6_). Upon study completion, all participants will be provided with PDFs containing links to the resources from the CommonGround resources page and further support and crisis information.

### Measures and Outcomes

#### Overview

The measures and assessment time points for the CommonGround fRCT are illustrated in Table 1.

**Table 1 table1:** The schedule of enrollment, interventions, and assessments for the CommonGround feasibility randomized controlled trial.

		Study phase							
		Screening (T_1_)	Enrollment (T_2_)	Allocation (T_3_)	After allocation				Closeout (T_6_)
					T_4_	T_5_	T_6_		
**Enrollment**									
	Eligibility screening	✓	✓						
	Informed consent	✓	✓						
	Randomization			✓					
**Interventions**									
	Intervention—CommonGround peer support platform				✓	✓	✓		
	Control—NHS^a^ mental health web pages				✓	✓	✓		
**Assessments**									
	PHQ-8^b^	✓	✓			✓		✓	
	WEMWBS^c^		✓					✓	
	GAD-7^d^		✓					✓	
	SF-36^e^		✓					✓	
	SCS-R^f^		✓					✓	
	CDSES^g^		✓					✓	
	EQ-5D-5L		✓					✓	
	CSRI^h^		✓					✓	
	PAM-13^i^		✓						
	SoVC^j^							✓^k^	
	3-item entitativity questionnaire							✓^k^	
	MAUQ^l^							✓^k^	
	AEs^m^ and SAEs^n^					✓		✓	

^a^NHS: National Health Service.

^b^PHQ-8: Patient Health Questionnaire–8.

^c^WEMWBS: Warwick-Edinburgh Mental Well-Being Scale.

^d^GAD-7: Generalized Anxiety Disorder scale.

^e^SF-36: 36-Item Short Form Health Survey.

^f^SCS-R: Social Connectedness Scale–Revised.

^g^CDSES: Chronic Disease Self-Efficacy Scales.

^h^CSRI: Client Service Receipt Inventory.

^i^PAM-13: Patient Activation Measure.

^j^SoVC: sense of virtual community questionnaire.

^k^Assessment delivered to the intervention group only.

^l^MAUQ: mHealth App Usability Questionnaire.

^m^AE: adverse event.

^n^SAE: serious adverse event.

#### Participant Characteristics

At baseline, we will use web-based Qualtrics questionnaires to collect age, date of birth, gender, sex assigned at birth, ethnicity, long-term physical health conditions, technology and internet use, history of using peer support, attitude toward peer support, and engagement in mental health treatment. The Patient Activation Measure (PAM-13) will also be administered [40]. The PAM-13 will measure the extent to which our sample are more passive care recipients versus more actively engaged in their health care. The PAM-13 is widely used within the NHS and for those living with long-term conditions [41] and has been validated among older adults with multimorbidity [42] and in mental health care settings [43].

#### Feasibility Outcomes

The primary feasibility outcome is the number of participants recruited to the trial per week and in total via each recruitment route (as self-reported by participants). The other feasibility outcomes are (1) number of participants who consent to the eligibility screenings of those contacted by the research team via the consent to contact route (eg, Bioresources and Lambeth NHS Talking Therapies Service), (2) number of participants found to be eligible at first screening (T_1_) of those who consent to the eligibility screenings, (3) number of participants found to be eligible at T_2_ of the number screened at T_1_ and T_2_, (4) number of participants who provide consent to take part in the feasibility trial of those eligible at T_2_, (5) number of participants withdrawn from the trial of those randomized, and (6) number of participants who respond to the follow-up assessment at 3 months (postintervention time point; T_6_) of those randomized.

Table 2 shows the criteria that have been selected to assess the feasibility of the trial. For each criterion, thresholds for *green* (the future definitive trial is likely feasible), *amber* (it may be feasible if appropriate changes are made), and *red* (it is likely not feasible) are presented.

**Table 2 table2:** Feasibility criteria and associated thresholds to inform progression to a larger, future confirmatory randomized controlled trial.

Feasibility criteria	Green	Amber	Red
The number of participants randomized at T_2_^a^ (target: N=150 participants)	N≥120	N≥80	N≥40
Participants found to be eligible by T_2_ of those who consent to the eligibility screenings at T_1_^b^	≥30%	≥20%	≥10%
Participants responding to the follow-up assessment at 3 mo (postintervention time point) of those randomized (T_3_^c^)	≥80%	≥60%	≥40%

^a^Second eligibility screening, consent to trial, and baseline assessment.

^b^Recruitment, consent to take part in eligibility screenings, and first eligibility screening.

^c^Randomization.

#### Acceptability and Usability Outcomes

In the intervention arm only, the acceptability and usability of CommonGround will be measured via the following:

Perceived usability at the postintervention time point (T_6_) using the mHealth App Usability Questionnaire (MAUQ). The MAUQ has demonstrated reliability and validity to measure mobile health app usability [44].Qualitative data on the perceived acceptability and benefits of CommonGround to people living with long-term conditions who are experiencing subthreshold depressive disorder.

Platform adherence and use metrics will also be captured in the intervention arm only to provide insights into engagement. This will include the clicks and interactions of participants when accessing and using the CommonGround platform, specifically the (1) number of times logging into the platform (in total, per day, and per week), overall and by device type (eg, mobile and desktop); (2) time spent logged in (in total, per day, and per week), overall and by device type (eg, mobile and desktop); (3) number of original posts created in the community feed, comments on posts, reactions to posts, and searches; (4) number of user-to-user interactions, including follows and unfollows, muting, viewing other users’ profiles, and posts flagged; (5) number of posts edited or deleted by moderators and time spent moderating; and (6) number of times participants download or open resources and save content to the My Garden private page.

#### Clinical and Health Economic Outcomes

Clinical outcomes will be measured for all participants at baseline (T_2_) or the postintervention time point after the 3-month intervention period (T_6_). All clinical outcomes will be treated as exploratory as this feasibility trial is not powered to evaluate clinical efficacy. These outcomes are (1) incidence of probable major depressive disorder at the postintervention time point only (T_6_), measured using the PHQ-8 [30] (PHQ-8>9=1; PHQ-8≤9=0); (2) symptoms of depression at the midintervention (week 6; T_5_) and postintervention (T_6_) time points, measured using the PHQ-8 total score [30]; (3) well-being at the postintervention time point (T_6_), measured using the Warwick-Edinburgh Mental Well-Being Scale [31]; (4) symptoms of anxiety at the postintervention time point (T_6_), measured using the Generalized Anxiety Disorder scale total score [45]; (5) health-related quality of life at the postintervention time point (T_6_), measured using the 36-Item Short Form Health Survey [46]; (6) social connectedness at the postintervention time point (T_6_), measured using the Social Connectedness Scale–Revised [47]; (7) self-efficacy in managing their health at the postintervention time point (T_6_), measured using the Chronic Disease Self-Efficacy Scales [48]; and (8) sense of virtual community at the postintervention time point (T_6_), measured using the sense of virtual community questionnaire [49] and an adapted 3-item entitativity measure [50,51].

The following measures will be used for the health economic outcomes:

The EQ‐5D‐5L, a standardized measure of health status consisting of 5 dimensions [52]. Standard value sets are summarized using a single index value determining the valuation of health-related quality of life [53].The Client Service Receipt Inventory [54]. We will use an adapted version of the Client Service Receipt Inventory that measures services and supports that a participant may have used over the previous 3 months. Subsections include accommodation and living situation, employment history, health care service use, and informal support.

#### Qualitative Outcomes

A nested qualitative study will be conducted for this feasibility trial. Within 6 weeks after the intervention (T_6_), a selection of participants will be invited to schedule a qualitative interview. For those who were in the intervention arm, the interviews will investigate their experiences and views on the peer support platform, examining the acceptability of the intervention and its perceived benefits and limitations in relation to the preconditions for change identified in the theory of change model. For all participants, the acceptability of trial procedures, including views on randomization and the relevance and burden of outcome measures, will also be explored. For those who were in the control arm, their perspectives on the acceptability of the control condition will be explored. Interview topic guides will be coproduced with our PPI group and coapplicant with lived experience. The online interviews will be audio recorded to enable transcriptions to be produced. The interviews will be conducted with approximately 40 individual participants (30 from the intervention arm and 10 from the control arm), which we estimate will afford sufficient information power [55].

The moderation team will also be invited to participate in an online focus group to explore their experiences moderating the CommonGround platform during the intervention period in accordance with the policies. Capturing moderators’ experiences will provide a unique perspective on how users interact with the platform. It will also provide insight into any safeguarding issues or risks and their management to inform future iterations of the trial and the associated moderation policies and procedures.

### AE Management

AEs and SAEs will be captured throughout the 3-month trial period. This includes the following:

Via a self-report questionnaire administered to participants in both arms at the midintervention (6 weeks; T_5_) and postintervention (12 weeks; T_6_) time points. This includes self-reporting of experiences of a list of expected AEs that we will coproduce with our PPI group.Through monitoring and recording any other SAEs and AEs that occur throughout the intervention period.As per recommended guidance on assessing the safety of digital health interventions [56] monitoring depressive symptom deterioration (as per the PHQ-8 score). The progression from mild depressive symptoms at baseline (score of 5-9) to either moderate (score of 10-14) or moderately severe (score of 15-19) depressive symptoms will also be classified as an expected AE. Progression to severe depressive symptoms (score of ≥20) will be classified as an expected SAE.

The AE protocol for this feasibility trial, including definitions, categorizations for expectedness and relatedness, and reporting procedures will be published elsewhere. Adequately capturing AEs and SAEs among a sample living with long-term conditions and subthreshold depressive disorder is important given that certain events (eg, hospitalization) are more likely to occur in our sample than in a healthy sample.

### Nonadherence

In the intervention arm, nonadherence to the CommonGround intervention will be assessed based on those who (1) are randomized to the intervention arm but do not create an account, (2) create an account but do not log in, or (3) log in less than once a month. In the control arm, nonadherence will be assessed through self-report, where participants will be asked whether they accessed the NHS mental health web pages. In both arms, reasons for nonadherence will be explored in the qualitative interviews. Nonadherence to completion of the baseline, midintervention, and 3-month follow-up questionnaires will be considered if participants do not respond to or complete the questionnaires.

### Data Management and Trial Monitoring

The procedures to maintain participant confidentiality will be outlined in the participant information sheet before consent. All individuals who complete the eligibility screenings will be randomly assigned a unique ID. Those randomized to CommonGround will be anonymous to other participants under their chosen pseudonym usernames. Such anonymity will be enforced by the moderation team, who will remove personally identifiable information from any forum posts or comments. Participants will be notified that anonymity may be broken by the research team under the circumstances required by the moderation and safeguarding policies (eg, disclosure of intent to commit terrorism offense or safeguarding concerns). Any use metrics or CommonGround account data shared between the software developer (Bitjam; data processor) and KCL (data controllers) external to the CommonGround platform will be pseudoanonymized (using the unique study IDs). Interview audio recordings will be shared securely with a transcription service and deleted thereafter. Platform data, data extracted from Qualtrics, and interview audio recordings or transcripts will be password protected and stored on secure servers.

A trial steering committee (TSC) will be formed, including an independent chair and independent members, the principal investigator, and the trial manager and statistician. The TSC will meet 3 times during the trial. For data monitoring purposes, we will also have an executive committee (with a single external member) who will review safety information (AEs and SAEs split by arm) and make recommendations to the blinded TSC chair, including recommendations regarding the continuation of the trial at the midintervention time point (T_5_).

### Statistical Analysis

We will follow the CONSORT (Consolidated Standards of Reporting Trials) 2010 statement extension for randomized feasibility and pilot trials [57] For this protocol, we have followed the SPIRIT (Standard Protocol Items: Recommendations for Interventional Trials) checklist (Multimedia Appendix 5). We will describe feasibility outcomes, use metrics, and clinical outcomes using appropriate summary statistics (eg, mean and SD, median and IQR for normally distributed continuous outcomes, and counts and proportions for categorical outcomes). As the clinical outcomes have been selected for their relevance for informing potential effect sizes for a future confirmatory trial, regression models will be used to estimate the effect of treatment allocation on outcomes measured at the postintervention time point (T_6_). The analysis of clinical outcomes will follow a modified intention-to-treat principle. All eligible, randomized participants with a recorded outcome (ie, the outcome is not missing) will be included in the analysis and analyzed according to the treatment to which they were randomized. For binary outcomes (incidence of probable major depressive disorder at the postintervention time point), we will conduct a binary logistic regression where the model includes terms for treatment allocation (peer support platform=1; control arm=0), the baseline severity minimization factor (high=1; low=0), and the baseline value of the outcome. If the binary outcome of major depressive disorder is common (eg, >20%), we will consider robust Poisson models instead, following the work by Zou [58]. For linear outcomes (eg, symptoms of depression at the postintervention time point), we will use linear regression with the same covariates. Exploratory treatment effects will be estimated based on the coefficients for treatment allocation; 95% CIs will be estimated using bootstrapping. Given the sample size and purpose of this feasibility trial, all estimates of treatment efficacy will be treated as underpowered and not used as the basis for inferential statements. To inform sample size estimation for a future confirmatory trial, we will calculate the SD of the continuous clinical outcomes.

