**Figure 1 figure1:**
[figure not shown]
Flowchart showing the participant timeline from recruitment (T1) to the end of data collection (T6). GP: general practitioner; HCP: health care professional; IAPT: Improving Access to Psychological Therapies; IMPARTS: Integrating Mental and Physical Healthcare: Research Training and Services; KCL: King’s College London; KHP: King’s Health Partners; LTC: long-term physical health condition; NHS: National Health Service; PHQ-8: Patient Health Questionnaire–8; PIS: participant information sheet; PTSD: posttraumatic stress disorder.

Following the baseline assessment (T_3_), participants will be randomly assigned (2:1) to the CommonGround platform or the control group. The intervention period will begin on the trial launch date (T_4_). At T_4,_ the control group will receive the first email sharing the NHS mental health web pages. For the intervention group, all accounts will be activated after the research team has verified their identity. Any accounts created after the launch date will be activated as soon as feasible. All participants will then have access to their treatment allocation for 3 months and can choose to engage as frequently as they wish. The control group will receive fortnightly emails resharing the links to the NHS mental health web pages throughout the intervention period.

At the midintervention time point (6 weeks; T_5_), participants will be invited to complete a short online questionnaire via individually generated Qualtrics links. Symptoms of depression (via the PHQ-8) and experiences of AEs and serious AEs (SAEs) will be recorded. Participants will have 2 weeks to respond to the midintervention questionnaire. The research team will send up to 2 email reminders and follow up via telephone if required.

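### The T6 models are complete-case and do not use the 6-week PHQ-8, so MDD incidence and the PHQ-8 SD may be understated, and the treatment effect is biased if dropout on worsening differs by arm

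*Protocol article*

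**What the plan says.** The Statistical Analysis section calls the approach modified intention-to-treat and defines it: "All eligible, randomized participants with a recorded outcome (ie, the outcome is not missing) will be included in the analysis", each analysed in the arm assigned. For continuous outcomes: "For linear outcomes (eg, symptoms of depression at the postintervention time point), we will use linear regression with the same covariates". Besides allocation, those covariates are "the baseline severity minimization factor (high=1; low=0), and the baseline value of the outcome". MDD incidence (PHQ-8 above 9 at T6) gets a logistic or robust Poisson model on the same basis.

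At 6 weeks both arms are sent a short questionnaire (Participant Timeline and Study Procedures): "Symptoms of depression (via the PHQ-8) and experiences of AEs and serious AEs (SAEs) will be recorded". The Clinical and Health Economic Outcomes section lists as an outcome "symptoms of depression at the midintervention (week 6; T_5_) and postintervention (T_6_) time points, measured using the PHQ-8 total score". The T5 score also falls under the descriptive summaries of clinical outcomes, and under AE Management a rise out of the baseline range counts as an adverse event.

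No dropout rate is forecast. Table 2 sets progression cuts for "Participants responding to the follow-up assessment at 3 mo (postintervention time point) of those randomized": green from 80%, amber from 60%, red from 40%.

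The third objective is to obtain parameters for the confirmatory sample size: MDD incidence, the SDs of PHQ-8 and the well-being scale, and preliminary effects.

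**The concern.** A participant with a T5 score but no T6 score contributes nothing to the T6 effect, incidence or SD, although the T5 score carries information about the missing value. Someone who scores 10-14 at week 6 and then stops responding is recorded as an expected adverse event, yet is absent from both numerator and denominator of MDD incidence. The trial would hold evidence of deterioration and leave it out of the incidence estimate.

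The stake is the third objective. The estimates support no inferential statement, but they are meant to size the next trial. The restriction to observed T6 outcomes and the covariate list are stated in the article itself, so this concerns a method the protocol fixes rather than a detail left to an analysis plan that is not shown.

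**Working it through.** **The plan's own figures.** The protocol gives no figure for missing-data bias. Its one computed figure, 15 recruits per week (95% CI 12.7-17.6), reproduces: χ²(0.025; 300)/20 = 12.70 and χ²(0.975; 302)/20 = 17.60. It does not bear on this point.

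**Inputs from the protocol.** 100 vs 50 participants; retention 80% and 60% (Table 2); MDD defined as PHQ-8 above 9 at T6; model covariates as above. Missing T6 scores: 150 × 0.20 = 30 and 150 × 0.40 = 60. For the 125 actually randomised (Results section), 25 and 50.

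**Reasoning.** With equal SDs at T5 and T6 and correlation ρ, suppose selection shifts the completers' mean T5 score in an arm by δ. Their mean T6 score then shifts by about ρδ. Bias in the effect is about ρ(δ_platform − δ_control). It cancels when both arms are selected alike and have the same T5 distribution. Incidence and SD are computed within arms, so nothing cancels there.

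**Simulation A (assumptions, not from the protocol).** SD 3.8, ρ = 0.6, no true effect, log-odds of dropout rising by up to 0.3 per T5 point.
- Incidence: about 25% becomes about 21% at 80% retention and 18% at 60%.
- Effect, same mechanism in both arms: bias 0.
- Effect, slopes 0.3 (platform) and 0.2 (control): about −0.1 at 80% and −0.2 at 60%.
- Effect, slope 0.3 in the platform arm and 0 in control: about −0.4 at 80% and −0.8 at 60%.

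**Simulation B (assumptions).** Baseline uniform on 5-9, residual SD 4, ρ = 0.6, true effect about −1.4, log-odds of dropout 0.3 per point of worsening by week 6, T5 observed for every T6 non-responder. Each cell reads full data → planned complete-case → using T5.

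| Retention; dropout on worsening in | Effect | Platform incidence, % | Control incidence, % |
|---|---|---|---|
| 80%; both arms | −1.39 → −1.33 → −1.40 | 16.6 → 13.6 → 16.4 | 27.1 → 22.9 → 27.2 |
| 60%; both arms | −1.39 → −1.28 → −1.38 | 16.6 → 11.3 → 16.2 | 27.1 → 19.5 → 26.9 |
| 80%; platform only | −1.40 → −1.85 → −1.40 | 16.7 → 13.5 → 16.6 | 27.2 → 27.2 → 27.1 |
| 80%; control only | −1.40 → −0.87 → −1.38 | 16.7 → 16.7 → 16.5 | 27.3 → 22.7 → 27.3 |

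With dropout on worsening in both arms, the SD of 3.92 becomes 3.79 at 80% retention and 3.69 at 60%. Varying ρ from 0.4 to 0.8, a control incidence of 27% reads 21-25% at 80% and 17-23% at 60%. One-arm bias in the effect is then 0.3-0.7 and 0.5-1.2 points.

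**If half of the T6 non-responders also lack T5 (simulation B, 80% retention).**
- Control incidence, dropout on worsening in both arms: 27.1 → 22.9 → 25.2, so (25.2 − 22.9)/(27.1 − 22.9) = 55% of the bias is removed.
- Effect, dropout on worsening in control only: −1.39 → −0.87 → −1.16, so 0.29/0.52 = 56% is removed.

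**Scale.** The standard error of the effect with SD 3.9 is 3.9 × √(1/80 + 1/40) = 0.76 at 80% retention and 3.9 × √(1/60 + 1/30) = 0.87 at 60%.

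**Illustrative future N** (1:1, 90% power, two-sided 5%). For a 40% relative reduction, n per arm = [1.96√(2p̄q̄) + 1.282√(p₁q₁ + p₂q₂)]²/(p₁ − p₂)². Total N is 602 at control incidence 27.2%, 746 at 22.9% and 906 at 19.5%. For a 1-point PHQ-8 difference, total N is 4 × (SD × 3.242)²: 646, 604 and 574 at SD 3.92, 3.79 and 3.69.

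**The case against.** **Limited consequence.** All clinical outcomes are exploratory and no efficacy inference will be drawn. Even one-arm dropout at 80% retention biases the effect by roughly half a standard error. An incidence near 22% on 80 people has a margin of 1.96 × √(0.22 × 0.78/80) = 9 percentage points, wider than the bias. Understated incidence also raises the future N, which is the cautious direction. This stands as a limit on severity. It does not remove the point: sampling error is shown in a confidence interval and this bias is not, and the understated SD lowers N.

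**T5 may be missing too.** Vouchers are paid at baseline and postintervention only (Ethical Considerations), and the T5 response window is 2 weeks against 4 at T6. This stands, and it caps what the remedy can do. T5 exists for PHQ-8 alone, so a repeated-measures model does not help the other T6 outcomes, including the well-being scale.

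**Stronger readings.** A reader might infer that the effect is biased whenever participants who worsen drop out. It is not: under a common mechanism the bias is zero without a true effect, and small with one. Arm-specific dropout is plausible with unblinded and very different arms, but nothing in the protocol shows it. Nor is T5 ignored altogether, since it is summarised descriptively and used for adverse-event monitoring; only the T6 models omit it. The modified intention-to-treat label does not mislead, because its definition follows at once. Finally, an unseen analysis plan may contain missing-data sensitivity analyses, so their absence from the article is no finding.

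**Conclusion.** The point holds in limited form. The protocol states a complete-case T6 analysis that leaves the 6-week PHQ-8 out of its models, and a better use of data already requested is available. If participants who are worse at week 6 drop out, T6 MDD incidence is understated by about 4 percentage points at 80% retention and 7 at 60% (from 25%), and the SD by about 3% and 6% (0.13/3.92 and 0.23/3.92). Material bias in the effect needs the further condition that such dropout differs by arm. These sizes rest on assumed SDs, correlations and dropout slopes; only the retention levels come from the protocol. The change is worth making because incidence and SD are named outputs of the trial. It is not a threat to any efficacy conclusion, since none is planned.

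**What to change.** 1. Estimate the PHQ-8 effect with a repeated-measures model on T5 and T6, with terms for arm by time, baseline PHQ-8 and the severity factor, including everyone with at least one follow-up score. Read the T6 contrast from it.
2. Estimate T6 MDD incidence by multiple imputation within arm, with T5 PHQ-8 as a predictor. Take the T6 PHQ-8 SD from the same imputed data.
3. Report the planned complete-case model alongside as sensitivity, and tabulate T5 against T6 response by arm so that readers can see how far T5 can help.

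Quantitative data collection ended in October 2024 (Results section), so label the added analysis as such and date it.

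Cost: slightly more analysis work and no new data. The method relies on missing-at-random given T5 and helps only where T5 was answered; roughly half or a little more of the bias is removed if half of the T6 non-responders also lack T5. All estimates stay exploratory.
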